### Study intervention

The MEDEA intervention is based on the telephone-based weight loss program that was standardized as part of BWEL [47].

#### Health education program (arms 1 and 2)

All patients in both the health education control and the intervention group receive a standardized Health Education Program focusing on healthy living. This includes a welcome letter, paper brochures, and links to websites focused on cancer-related topics. Covered themes include healthy eating, exercising, nutrition, and cancer.

In addition, all study participants receive a quarterly newsletter with additional materials, including invitations to join webinars/conferences that focus on breast cancer and other health topics (e.g., treatment updates in breast cancer, management of specific side effects, general cancer screening). Finally, patients are provided with updates about study and enrollment progress.

#### Weight loss intervention (arm 2)

Patients randomized in the interventional arm of MEDEA receive behavioral support to facilitate lifestyle change based on caloric restriction and increased PA, delivered remotely by a weight loss coach. Personalized coaching is crucial for the MEDEA intervention; therefore, participants are paired with an individual coach who works with them through all phases of the weight loss program. Lifestyle coaches are required to have expertise in diet/nutrition and received initial training in behavioral change, PA, and/or weight loss in cancer patients.

The behavioral change program is based on the social cognitive theory, which hypothesizes that the interactions between environmental, personal, and behavioral elements determine behavioral change [59].

The intervention is implemented through 24 semi-structured and standardized telephone calls, delivered over 1 year, supplemented by a detailed participant workbook that is mailed to participants after randomization. Participants are encouraged to review the content of the call beforehand using the workbook in order to facilitate the telephone interactions with their coach. Calls are scheduled at the participant’s convenience. Each call lasts approximately 30 min, although the first four calls last longer (up to 45–60 min). Calls are scheduled as follows: intensive phase (weeks 1–12; 12 weekly calls), consolidation phase (weeks 13–24; six bi-weekly calls), and maintenance phase (week 25–end of intervention; one monthly call). Every effort is made to ensure that a core of 16 calls (the minimum number required to ensure the success of the intervention) take place during the first 6 months and that the frequency is greatest early in the intervention, when participants are making the most rapid changes. However, the intervention is considered to be completed if at least 16 calls are completed over 1 year. Table 2 outlines the 24 telephone calls with respective thematic content. A call is considered completed if the specific thematic content is approached and delivered. Notwithstanding standardization of the intervention, because of the focus on behavioral change and not to increase patient burden, the study allows flexibility in the approach taken with individual participants. This flexibility is reflected in adjusting calls scheduling by accommodating, for example, for vacations or personal/family plans, and by tailoring thematic content. In general, if one or more calls are skipped, thematic contents regarding caloric intake and ways to improve PA are prioritized when calls are resumed, in order to reinforce key messages and facilitate participants to meet dietary and activity goals and make the changes recommended as part of the intervention.

**Table 2 Tab2:** MEDEA telephone-based intervention sessions: schedule and thematic content

Intervention phase	Phone call	Week	Title	Thematic content
**Intensive phase:** weekly calls	**1**	1	Welcome to the MEDEA program	Introduction to program
	**2**	2	Getting started: tipping the calorie balance	Caloric restriction
	**3**	3	Not all fats are created equal: eat less of most, more of some	Caloric restriction
	**4**	4	Cutting calories by controlling your portions	Caloric restriction
	**5**	5	Move those muscles!	Physical activity
	**6**	6	Working with what’s around you: cue control	Behavioral support
	**7**	7	Problem solving	Behavioral support
	**8**	8	Being active: a way of life	Physical activity
	**9**	9	Healthy eating	Caloric restriction
	**10**	10	Healthy eating and breast cancer	Breast cancer and nutrition
	**11**	11	Preparing a better breakfast, lunch, and dinner	Caloric restriction and Behavioral support
	**12**	12	Summary and progress review	Summary and evaluation
**Consolidation phase:** bi-weekly calls	**13**	14	Talk back to negative thoughts	Behavioral support
	**14**	16	The slippery slope of lifestyle change	Behavioral support
	**15**	18	Stepping up your physical activity	Physical activity
	**16**	20	Ten ways to control your hunger	Behavioral support
	**17**	22	Handling holidays, vacations, and special events	Behavioral support
	**18**	24	Taking stock and celebrating your success	Summary and evaluation
**Maintenance phase:** monthly calls	**19**	28	Ways to stay motivated	Behavioral support
	**20**	32	Recovering from overeating	Behavioral support
	**21**	36	Weight loss review	Caloric restriction
	**22**	40	Adapting to long-lasting success	Behavioral support
	**23**	44	Preparing for what comes next	Summary and evaluation
	**24**	48	Congratulations! You finished the MEDEA program!	Summary and evaluation

Lifestyle coaches individualize the call content as necessary to address individual problems (ensuring that key aspects of each call are covered) and are trained to address motivational and emotional issues as they arise, partnering with participants to overcome barriers to success. Data on compliance, changes in diet, PA, and weight reported by participants are captured and discussed with coaches during the calls. Coaches prepare a brief written summary of motivational, behavioral, diet, and exercise issues discussed during each call.

A toolbox approach that allows for tailoring the intervention to the individual participant is available to facilitate reaching intervention goals and losing weight. Toolbox solutions also aim at optimizing the intervention to meet the needs of specific ethnic, socioeconomic, or other patient populations. Toolbox materials were partly developed by coaches during the preparation phase of the study and reviewed by the MEDEA Study expert board. Examples of MEDEA Toolbox solutions are listed in Table 3.

**Table 3 Tab3:** Examples of content for MEDEA Toolbox approaches

**Eating patterns and meal plans**	- High-protein/low-carb eating pattern - Mediterranean eating pattern
**Cooking and shopping tips**	- Using your hands to estimate portions - Weighing and measuring foods - Food shopping on a budget - Commercial protein bars - Meal prep and batch cooking
**Activity and symptoms**	- Three examples of resistance training - 50 ideas to increase daily steps - Apps, videos, books, and tutorials to exercise - Being active with neuropathy - Being active with joint pain - Being active with lymphedema
**Miscellaneous**	- Sports and cancer - Managing weight when you quit smoking - “Use” your hunger

The MEDEA Study schema and timeline are displayed in Fig. 2.

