### Study design

MEDEA is a RCT evaluating the effect of health education alone vs. weight loss intervention plus health education on CRF in overweight and obese women with early-stage breast cancer. Patients are offered to participate in this study during routine consultations. Participants are randomized to a standard health education program (arm 1 control) vs. a 1-year personalized telephone-based health education weight loss follow-up (arm 2 interventional). A permuted block randomization is applied in a 1:1 randomization ratio using a block size of 4. Stratification occurs on the basis of BMI at diagnosis (overweight [BMI 25.0–29.9 kg/m^2^] vs. obese [BMI ≥ 30.0 kg/m^2^]), age (≤ 50 vs. > 50 years), and receipt of endocrine therapy (yes vs. no) (Fig. 1).

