
### Statistical considerations

Previous meta-analyses indicated that exercise was more effective than control in reducing CRF, with a standardized effect size ~ 0.40 [31, 65–67], but there are limited data on the effect of lifestyle interventions aimed at weight loss on CRF among overweight or obese patients. To detect an effect size of 0.40, a sample size of 101 evaluable patients per arm will provide 80.0% power using a two-sided α = 0.05, two-sample test. The primary test statistic for inference is the time-by-treatment interaction effect in a linear mixed model. This effect size (0.40) is considered as small to moderate by Cohen [68]. Taking some potential drop-out into account, the final sample size for this study is inflated to 220 patients. The primary comparison of CRF among intervention assignments will be performed in the intent-to-treat population of all randomized patients (i.e., all analyses will retain each participant in the group he was randomly assigned regardless of missing data or drop-out status).

The primary analysis of MEDEA will compare the primary endpoint of CRF scores at the M12 post-randomization time point between arms. This comparison between arms will employ a linear mixed model with random patient effect using time as a categorical variable, treatment arm, and a treatment by time interaction with patient-reported CRF measured by appropriate EORTC QLQ-C30 subscale scores. In a sensitivity analysis, baseline characteristics will be added as fixed covariates to the model.

All other measures/time points/analyses will be considered secondary or exploratory analyses. Similar analyses as those specified for the primary endpoint will be performed for other scales. For binary endpoints, chi-squared tests will be used. Further analyses will include analyses of continuous endpoints using mixed-effects models and binary endpoints using generalized estimating equations. The analyses of objectives including IDFS as an endpoint are performed in an intention-to-treat manner.

For the primary analysis of MEDEA (primary endpoint of global CRF), two-sided *p*-values < 0.05 will be considered statistically significant. All other endpoints are considered secondary or exploratory, with no *p*-value adjustment for multiple testing. For interpreting the clinical significance of effects, 0.2, 0.5, and 0.8 standard deviation effects will be considered as small, moderate, and large, respectively [68].

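### Arm-2 patients are nested within coaches, but the primary model and the power calculation treat all patients as independent; if coaches differ, the primary standard error is too small

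*Protocol article*

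**What the plan says.** The section Weight loss intervention (arm 2) states that "participants are paired with an individual coach who works with them through all phases of the weight loss program". Implementation of study procedures confirms that this pairing follows randomization to the intervention arm; controls receive the health education program without a coach.

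Randomization is of individual patients: "A permuted block randomization is applied in a 1:1 randomization ratio using a block size of 4" (Study design).

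Statistical considerations describes the primary comparison at month 12 as a "linear mixed model with random patient effect using time as a categorical variable, treatment arm, and a treatment by time interaction". The one stated sensitivity analysis adds baseline characteristics as covariates. For sample size, "101 evaluable patients per arm will provide 80.0% power", "using a two-sided α = 0.05, two-sample test", for a standardized effect of 0.40. The step up to 220 is attributed to attrition alone: "Taking some potential drop-out into account, the final sample size for this study is inflated to 220 patients".

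The section on standardization and quality control describes common training for coaches, weekly supervision, central review of a 5% random sample of calls, and central feedback. The article does not give the number of coaches, a coach ICC or a design effect.

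**The concern.** This is a partially nested design: patients are randomized one by one, but in one arm only they are then grouped under a shared provider for a year and up to 24 calls. If some coaches get better results than others, patients of the same coach have correlated outcomes. The random patient effect deals with repeated measurements on one patient; it does not absorb correlation between different patients of the same coach.

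The article states the random-effects structure outright, so this is a stated choice and not merely a detail left to an analysis plan that is not shown.

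The target of inference also matters. The secondary objectives include dissemination and implementation in the French setting, and the Discussion aims at an intervention ready for wide clinical use. That treats the trial's coaches as a sample of those who would deliver the program later, so variation between coaches belongs in the standard error. At stake are the size and power of the trial's only confirmatory test.

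**Working it through.** **Inputs from the article (Statistical considerations):** standardized effect 0.40 (so SD = 1), two-sided α = 0.05, 80.0% power, n = 101 evaluable per arm, 220 randomized.

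**Inputs assumed, because the article does not give them:** number of coaches k = 5 to 10 and coach ICC = 0.01 to 0.05, with equal caseloads m = 101/k.

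**Step 1: the plan's own figure.** By the normal approximation, n = 2(1.960 + 0.842)²/0.40² = 98.1, so 99 per arm. At n = 101, power is 81.1% by the normal approximation and 80.8% by the noncentral t with 200 df. The plan's figure therefore reproduces with independent patients and a design effect of 1. The increase from 202 to 220 allows for 18/220 = 8.2% drop-out and nothing else.

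**Step 2: variance with coach clustering in arm 2 only.**
- Arm-2 design effect: DE = 1 + (m − 1) × ICC
- Variance of the difference relative to independence: R = (1 + DE)/2
- True SE divided by model SE: √R
- Actual two-sided error: 2[1 − Φ(1.96/√R)]
- Power of a test using the correct SE: noncentral t with noncentrality 0.40/√((1 + DE)/101), first with 200 df, then with Satterthwaite df = (v₁ + v₂)²/[v₁²/100 + v₂²/(k − 1)], where v₁ = 1/101 and v₂ = DE/101

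**Step 3: two worked cases.**
- 10 coaches, ICC 0.01: m = 10.1; DE = 1 + 9.1 × 0.01 = 1.091; R = 1.046; √R = 1.022. Satterthwaite df is about 31.
- 5 coaches, ICC 0.05: m = 20.2; DE = 1 + 19.2 × 0.05 = 1.96; R = 1.48; √R = 1.217. Satterthwaite df is about 9.

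| Coaches | ICC | DE, arm 2 | SE ratio | Two-sided error | Power, 200 df | Power, Satterthwaite df |
|---|---|---|---|---|---|---|
| any | 0 | 1.00 | 1.00 | 5.0% | 80.8% | depends on k |
| 20 | 0.01 | 1.04 | 1.01 | 5.2% | 80% | 79% |
| 10 | 0.01 | 1.09 | 1.02 | 5.5% | 79% | 77% |
| 6 | 0.02 | 1.32 | 1.08 | 6.9% | 75% | 70% |
| 5 | 0.02 | 1.38 | 1.09 | 7.3% | 74% | 66% |
| 5 | 0.05 | 1.96 | 1.22 | 10.7% | 64% | 55% |

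The 20-coach row lies outside the assumed range and shows how the problem fades as coaches increase. The last column also includes the price of estimating a coach variance from few coaches.

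**Step 4: simulation check.** In 20,000 simulated two-arm trials per setting, analysed as a simple month-12 comparison that ignores coach, the rejection rate under a zero average effect was 5.5% (10 coaches, ICC 0.01) and 6.9% (6 coaches, ICC 0.02). Both agree with the formula.

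**The case against.** The strongest reply has four parts.

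1. **The deciding inputs are unknown.** A reader might infer that the primary standard error is certainly too small and that power is certainly below 80%. The article does not support that: without the number of coaches and the ICC, neither can be asserted. With 20 coaches and ICC 0.01 the error is 5.2% and power about 80%. This stands, so the point is conditional.

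2. **The type I error claim depends on the null hypothesis.** Patients are randomized individually. If coaching changes no patient's fatigue, coaches cannot differ in their effect, no coach-induced correlation arises, and the planned test keeps its 5% level. Inflation needs coaches who truly differ while averaging to no effect, with inference extended beyond these coaches. If the coaches are regarded as fixed, the standard error is not understated on this ground. This also stands. The second condition is nevertheless the natural reading of a trial that aims at dissemination.

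3. **A coach effect is not shown to be expected.** A reader might infer one from the emphasis on personalized coaching and the freedom to tailor calls. But the tailoring described responds to the patient's circumstances, with the key content of each call still covered; that is not the same as coaches differing from one another. A coach effect is plausible, not established.

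4. **Delivery is standardized.** Training, weekly supervision, call review and a common workbook all aim to make coaches alike and may lower the ICC. They do not show it to be zero, and they do not enter the model.

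It is also fair to say that with few coaches the variance component is poorly estimated and the small-sample correction costs power. Making the coach model the sole primary analysis is therefore debatable.

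**Conclusion.** The point holds in conditional form. The nesting in arm 2 and the independence assumed in both the model and the sample size are plain in the text. If the coach ICC is above zero and the result is meant to reach beyond this trial's coaches, the planned analysis overstates the precision of the arm-2 mean.

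Across the assumed range of 5 to 10 coaches and ICC 0.01 to 0.05, with 101 evaluable patients in arm 2, the effect runs from negligible to material. At the mild end the two-sided error is about 5.5% and power about 79% (77% with small-sample df); at the severe end the error is about 11% and power about 64% (55%). These are illustrations under assumed inputs, not estimates for this trial. The documents do not show that the error rate is in fact inflated, only that the plan would neither detect nor allow for it.

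**What to change.** - Carry the coach identifier into the analysis data set.
- Pre-specify, at least as a key sensitivity analysis of the month-12 comparison, a partially nested model: the planned fixed effects and patient effect, plus a random coach effect in arm 2 only, with each control treated as a singleton, and Satterthwaite or Kenward-Roger degrees of freedom.
- Report the number of coaches and the estimated coach ICC with its interval.
- State beside the sample size that 80% power assumes no coach clustering.

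The cost is wording in the analysis plan plus one variable. Pairing is known from call scheduling, and Table 1 already plans call completion by coach. The downside is a wider interval and, with few coaches, an imprecise variance component. The trial status section says that accrual was completed in 2021, so the sample size cannot be changed on this ground; the analysis and the reporting are what can be changed.

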**Fig. 2 Fig2:**
[figure not shown]
MEDEA Study schema and timeline. M, month

#### Intervention goals

MEDEA Study goals include the following:
Weight loss: weight loss ≥ 10% of baseline (0.5–1.0 kg per week) until a BMI no less than 21 kg/m^2^.Caloric restriction: caloric deficit of 500–1000 Kcal per day based on current weight and weight loss target. Recommended calorie levels are based on body weight and standardized tables: calorie levels range from 1200 to 1499 kcal/day for participants weighing < 110 kg at baseline and 1500–1800 kcal/day for individuals weighing ≥ 110 kg at baseline. Caloric goals are modified as necessary to assist participants in reaching their goals. The basic diet used in the MEDEA materials supports a low-fat, high-fruit and vegetable diet.PA: the primary focus of the PA portion of the weight loss intervention will be on moderate-intensity aerobic activity. Gradual increase in moderate-intensity aerobic activity has a target goal of 150 min/week during the initial phase of the intervention and 225–300 min/week in the maintenance phase of the intervention.

#### Standardization of the intervention and quality control

Approaches to standardization of the intervention include the following: (1) A standardized training protocol for the coaches that was piloted in the BWEL study was developed by the MEDEA and BWEL investigators. Training involved the use of printed materials (e.g., protocol, coach’s manual, and a sample of call scripts) and in-person activities (e.g., behavioral/motivational interviewing techniques, role playing, review of telephone tapes). (2) Standardized supervision of coaches: regular meetings with coaches and the MEDEA Study board and coordinators are held on a weekly basis to review progress and troubleshoot problems associated with the delivery of the intervention. Coaches have the ability to discuss their calls summary and to receive feedback on relevant aspects of their interactions with study participants. Regular participation of lead nutrition, exercise, and behavioral experts to MEDEA meetings is assured to address specific issues. (3) Recording and centralized review of 5% randomly selected phone calls: these calls are reviewed by the MEDEA Study board and coordinators with the coaches for adherence to the study intervention, and standardized feedback is provided to the individual coaches. (4) Centralized calculation of individual weight. (5) Centralized response to diet and PA problems arising between telephone calls. Participants are provided with contacts of the MEDEA Study coordinators, to alert study personnel of issues that develop during participation in the intervention. Medical problems are referred to the participants’ treating oncologist or generalist. (6) Centralized feedback system: coaches have the ability to refer to the MEDEA team at any time for questions and to troubleshoot problems arising during the delivery of the intervention, through a centralized e-mail managed by a dedicated study manager.

### Study measures

The MEDEA Study assessments include a baseline (M0) assessment (at time of enrollment), two “on-health education-intervention visits” (M6 and M12), and a final follow-up visit (M18). Participants undergo study visits at their local site. Collected measures include CRF, quality of life, depression and anxiety, health behaviors, anthropometric measures, cost-effectiveness measures, assessment of disease status and adverse events, adherence, and satisfaction with the study intervention. Details about the study measure type and frequency of assessment are reported in Table 1.

All patients in MEDEA are provided with Actigraph accelerometers [60], recording the duration and intensity of PA. Readings are obtained centrally through the use of the ACTILIFE software [61]. Participants do not receive any feedback from the accelerometer unit, regardless of the study arm. Participants wear the accelerometer for 7 days at all four time points (M0, M6, M12, and M18). Accelerometers are mailed to participants by the study manager along with an instruction sheet regarding its use and a diary form to indicate the dates that the accelerometer was worn. Participants return the accelerometer to Gustave Roussy site along with a pre-addressed return mailer. For the first visit, they wear the accelerometer before the start of the intervention if randomized to arm 2. For subsequent assessments, a pre-paid mailer is included in the packet so that participants can directly return materials to Gustave Roussy. Dietary assessment is performed using a 94-item food frequency questionnaire [62]. Weight assessments are performed by health care professionals in the clinic during follow-up visits.

Direct medical costs and indirect costs will be assessed from the perspective of the French national health insurance using data linkage to SNDS (“Système national des données de santé” – National Health data system [63]) database for each patient (indirect matching using the date of birth, zip code of the patient’s residence, type/date/hospital identification code for any breast cancer treatment, health insurance characteristics). Resource use includes all-cause hospitalizations (distinguishing between breast cancer-related hospitalizations and hospitalizations for other causes), all drugs consumption, and sick leaves. QALYs are measured using utility values derived from the Euroqol-5D (EQ-5D-3L) [64] at all four time points (M0, M6, M12, and M18).

Participants in both study arms are asked about the following musculoskeletal events during each follow-up visit: fractures, sprains, tendon or ligament injuries, and orthopedic surgeries. Non-solicited adverse events such as post-surgical wound infections or side effects from hormonal therapy such as hot flashes are not required to be reported for this trial.

Adherence to the intervention is measured by the number of completed phone calls/total number of calls scheduled. To define the intervention as completed, a minimum of 16 calls have to be completed. Satisfaction with the intervention will be also assessed with qualitative analyses and dedicated focus groups.

IDFS is defined as the time from randomization to any one of the following: distant, invasive, or locoregional recurrence; ipsilateral or contralateral invasive breast cancer; second primary invasive cancer (non-breast cancer other than basal or squamous cell carcinoma of the skin that has been adequately treated, and carcinoma in situ of the cervix); or death from any cause. Overall survival is defined as the time from randomization to death from any cause. Patients who withdraw consent to be followed are censored at that time point, and patients who are lost-to-follow-up are censored at the time point they were last determined to be disease-free.

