#### Secondary objectives

Secondary objectives of MEDEA include the following: secondary objective 1—the evaluation of the impact of the weight loss intervention on (1.1) specific CRF dimensions, including physical, emotional, and cognitive CRF; (1.2) QOL, including domains such as global health status, emotional, social, role, cognitive function, insomnia, pain, body image, and systemic therapy side effects; (1.3) sleep quality; and (1.4) anxiety and depression, weight and BMI, dietary habits and quality, and PA; secondary objective 2—the dissemination/implementation of the intervention, adapted from a US setting, in the French health care setting; secondary objective 3—health care costs (hospital admissions, all-drug consumption, sick leaves), cost-effectiveness (cost per quality-adjusted life-year QALY), and patient motivation and satisfaction; and secondary objective 4—adverse musculoskeletal events including fractures, sprains, tendon, or ligament injuries, and orthopedic surgeries are assessed (safety).

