#### Withdrawal criteria

Premature discontinuation of study intervention does not necessarily mean the patient prematurely discontinues its participation in the study. (1) Withdrawal criteria from study intervention. A patient will not receive any further study intervention if any of the following occurs: request from the patient not to receive further intervention; withdrawal of consent, or lost to follow-up; adverse events or any condition incompatible with the continuation of the study intervention according to the judgment of the investigator; any medical event requiring administration of an unauthorized concomitant treatment; pregnancy or intent to become pregnant; subject non-compliance to study procedures that in the investigator and/or sponsor judgment warrants withdrawal; study terminated by the sponsor; patients with disease recurrence at any site, or new invasive cancer diagnosis, can continue the intervention if they wish, and if it is considered appropriate by physician discretion. Patients who are withdrawn from further receipt of study intervention will continue to have *follow-up visits.* (2) Withdrawal criteria from the trial. Reasons for withdrawal from the trial may include lost to follow-up, consent withdrawn, disease recurrence or new invasive cancer diagnosis, and death.

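### The safety objective covers exercise-type injury only, and the reporting waiver makes no exception for events related to the intervention or ending it, so an absence of reported dietary harm would be uninformative

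*Protocol article*

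**What the plan says.** All references are to the protocol article.

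- **Secondary objectives.** Objective 4 is the only safety objective: "adverse musculoskeletal events including fractures, sprains, tendon, or ligament injuries, and orthopedic surgeries are assessed (safety").
- **Study measures, events solicited.** Participants in both arms are "asked about the following musculoskeletal events during each follow-up visit: fractures, sprains, tendon or ligament injuries, and orthopedic surgeries". These are the categories of objective 4.
- **Study measures, waiver.** The next sentence reads: "Non-solicited adverse events such as post-surgical wound infections or side effects from hormonal therapy such as hot flashes are not required to be reported for" the study.
- **Study measures, opening paragraph.** Adverse events are listed, without restriction, among the measures collected, and the reader is sent to Table 1 for type and frequency. Table 1 has no adverse-event row.
- **Intervention goals.** The diet component is a "caloric deficit of 500–1000 Kcal per day based on current weight and weight loss target". The weight goal is "weight loss ≥ 10% of baseline (0.5–1.0 kg per week) until a BMI no less than 21 kg/m"².
- **Withdrawal criteria.** The intervention stops for, among other reasons, "adverse events or any condition incompatible with the continuation of the study intervention according to the judgment of the investigator". This is not confined to musculoskeletal events. Patients who stop remain in follow-up.
- **Data collection, management, and auditing.** The research assistant verifies adverse events and checks that reporting requirements are met. Those requirements are not reproduced.

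**The concern.** The intervention has two physical components, caloric restriction and increased activity. The solicited events match the activity component only, and no event of the kind a diet might cause is asked about. The waiver then releases sites from reporting anything that was not asked about.

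The waiver also sits badly with the withdrawal rule. An investigator may end the intervention for a non-musculoskeletal adverse event, yet the reporting rule does not say that this event must be reported.

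What is at stake is the safety conclusion, not the primary fatigue comparison. The Discussion hopes to help make weight loss support a standard of care. A safety section written from objective 4 alone could be read as covering the whole programme, when it can describe injury only.

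**Working it through.** The plan gives no figure for safety, so there is none to reproduce. The check sets the sections side by side, and the arithmetic only illustrates what a zero count can and cannot show.

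**1. Does the solicited list reach the diet component?**

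The list has fractures, sprains, tendon or ligament injuries and orthopedic surgeries. None is specific to a caloric deficit, so it does not.

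**2. Does the waiver except events related to the intervention?**

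Its two examples, surgical wound infection and hormonal-therapy effects, come from cancer treatment. They are introduced as examples and do not limit the class, which is all non-solicited events. No exception is stated for relatedness or for discontinuation.

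**3. Do the sections on adverse events agree?**

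| Section | What it implies |
|---|---|
| Withdrawal criteria | Any adverse event can end the intervention |
| Study measures, opening | Adverse events in general are collected; details in Table 1 |
| Table 1 | No adverse-event row |
| Study measures, waiver | Only the solicited musculoskeletal events are clearly required |
| Data collection, management, and auditing | Adverse events are verified against requirements not shown |

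The article does not settle whether a non-musculoskeletal event that stops the intervention must be reported.

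**4. What do other data capture, in both arms?**

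- All-cause hospitalizations, drug use and sick leave: collected as costs.
- Deaths: collected for overall survival.
- Nausea and vomiting, appetite loss, constipation and diarrhea: QLQ-C30 scores at M0, M6, M12 and M18.
- Anxiety and depression, weight and BMI: secondary outcomes at the same visits.

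None is named as a safety outcome. A dietary problem managed outside hospital may leave no identifiable trace. The section on standardization and quality control refers medical problems to the treating doctor and does not say that they enter the trial record.

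**5. What would a zero count mean?**

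Inputs: 220 patients, randomized 1:1, so 220 / 2 = 110 in the intervention arm.

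With complete capture and no events, the one-sided 95% upper limit is 1 − 0.05^(1/110) = 0.0269, about 2.7%.

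The chance of seeing at least one event is 1 − (1 − p)^110. The document gives no rates, so p is assumed:

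| Assumed true rate p | Chance of at least one event |
|---|---|
| 1% | 67% |
| 2% | 89% |
| 5% | 99.6% |

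Complete capture would therefore be informative at this sample size. Without solicitation or a duty to report, a zero count supports no such limit.

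**6. Which weight-based counts are usable?**

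Visits are six months apart, about 26 weeks. A mean loss above 1.0 kg per week between visits needs more than 26 × 1.0 = 26 kg, so that count could hardly detect anything. A BMI below 21 from the entry minimum of 25 needs a loss above (25 − 21) / 25 = 16%, against a goal of at least 10%. Such patients will probably be few, but clinic measurements can identify them.

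**The case against.** The strongest reply has four parts.

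*The waiver is aimed at cancer-treatment effects, and not being required to report an event does not mean that it goes unreported.* This stands. A reader might infer that dietary harms, and events that stop the intervention, go unreported, or that their rate is zero by rule. The documents do not support that. Sites may record such events, adverse events are listed as collected and verified, and nothing says that a stopping reason is left unrecorded.

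*Serious harm is largely captured elsewhere.* This stands in part. An event leading to admission should appear in the hospitalization data, and excessive weight loss in the clinic weights. These data are not assigned to the safety objective, and events managed outside hospital remain uncovered.

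*The article condenses a fuller protocol, where serious-event procedures, discontinuation forms and safety tables would normally sit.* This stands for those items, and their absence is no finding. It does not answer the point, because the article itself states the solicited list and the waiver.

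*The figures under Intervention goals are goals, and a targeted safety list is a legitimate choice in a pragmatic trial.* This also stands. A reader might take 0.5–1.0 kg per week and a BMI of 21 as safety limits that the trial fails to monitor. The article presents them as a target pace and an end-point for the weight goal. A targeted list is acceptable if the safety conclusion is equally targeted.

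**Conclusion.** The point holds in limited form. As stated, the safety objective can describe exercise-type injury only. The waiver has no exception for events related to the intervention or ending it, and the sections that mention adverse events do not fit together. Followed as written, an absence of reported diet-related harm would be uninformative: the limit of about 2.7% that 0 of 110 would give under complete capture could not be claimed.

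The gap is partial, because hospitalizations, deaths, symptom scores, weight and BMI are collected in both arms for other purposes. The primary efficacy analysis is unaffected. This is a cheap improvement, not a defect that threatens the trial. The verdict assumes that the full protocol does not already narrow the waiver. If it does, only the article's wording needs correcting.

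**What to change.** 1. In Study measures, confine the waiver to events unrelated to the intervention, keeping the present examples.
2. Require reporting of any adverse event that leads to stopping the intervention or trial participation. Only the intervention arm has coaching to stop, so the first part will be mainly descriptive.
3. Under secondary objective 4, tabulate by arm, as safety outcomes, the all-cause hospitalizations and deaths already collected. Add a descriptive count of patients with BMI below the 21 kg/m² named under Intervention goals. This counts departures from the plan's own figure and sets no clinical rule.
4. Reconcile Withdrawal criteria, both statements in Study measures, Table 1 and the monitoring section, so that they say the same about which adverse events are collected and reported.
5. If items 1 to 3 are not adopted, state that the safety conclusion is limited to musculoskeletal harm.

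**Cost.** Items 1 and 4 are wording. Item 3 uses data already planned and adds one table. Item 2 adds slightly to site reporting. Accrual was completed in 2021, so for patients already followed the reasons for stopping may have to be recovered from site records and may be incomplete.
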